## Recruitment and consent

The parents or legal representatives of 8-9 years old children who participate in the Dutch Vaccination Programme (RVP) will be informed about the study by mail (annex 1A). If they would like to participate in the study they will fill in a reply card. After receiving this card we will explain the parents about the study proposal schedule and (dis)advantages (patient information form (PIF), annex 1B) by telephone and mail. After at least one week a second telephone call will be made. If parents agree in participation, the in- and exclusion criteria will be checked and subsequently an appointment for the booster vaccination and blood sampling at the pediatric outpatient’s clinic in the Spaarne Hospital in Hoofddorp will be made. If the parents or legal representatives of the infant has given informed consent and meets all the criteria, he/she will enter the study as a participant, and will be given a Unique Trial Number (UTN). The case report form (CRF) (annex 2) contains a section for documenting the procedure of informed consent and must be completed by the investigator.

The principal clinical investigator will obtain signed informed consent from each volunteer that indicates that he/she is willing to participate in the study. The volunteers should have sufficient time to consider their decision or consult a third party. A copy of the text of the informed consent, in Dutch, will be submitted to the CCMO (annex 3).

During the visit the PIF will be reviewed and discussed with the investigator. After a written consent for participation is signed by both parents of the child, the blood sampling (15 ml) and the vaccination will be given. An appointment for the blood sample at 28 days (± 2 days) will be made.

During the second visit a blood sample of 15 ml will be taken. After 1 year the investigator will contact the parents again to make an appointment for the last visit at which another blood sample of 15 ml will be done.

The control group will be recruited from the children who were not able to participate at the start of the Booster study, because we had too many registrations. We will contact the parents of these children again by phone. In addition we will send a newsletter (annex 1) to each participant of the Booster study to inform about the progress of the study and in which we also call up for children who could participate in the control group of the Booster study.

## Objection by minors or incapacitated subjects (if applicable)

## Benefits and risks assessment, group relatedness

## Compensation for injury

According to a Ministerial Order, RIVM is excluded from compulsory insurance for clinical research as determined by the Dutch law on Medical Investigations (WMO, section 7, paragraph 6). Participants can recover the loss from RIVM. Any claims will be settled according to the terms of an insurance company. Participants will be informed about these terms in detail in the Participant Information Form.

The sponsor has a liability insurance which is in accordance with the legal requirements in the Netherlands (Article 7 WMO and the Measure regarding Compulsory Insurance for Clinical Research in Humans of 23rd June 2003). This insurance provides cover for damage to research subjects through injury or death caused by the study.

1. € 450.000,-- (i.e. four hundred and fifty thousand Euro) for death or injury for each subject who participates in the Research;
2. € 3.500.000,-- (i.e. three million five hundred thousand Euro) for death or injury for all subjects who participate in the Research;
3. € 5.000.000,-- (i.e. five million Euro) for the total damage incurred by the organisation for all damage disclosed by scientific research for the Sponsor as ‘verrichter’ in the meaning of said Act in each year of insurance coverage.

The insurance applies to the damage that becomes apparent during the study or within 4 years after the end of the study.

## Incentives (if applicable)

In public health view, participation in this study will contribute to the confidence in the Dutch Vaccination Programme. Children will receive a present of 10 euro after the first post-vaccination blood sample and 15 euro after the second post-vaccination blood sample for their participation.

Children who participate in the control group will receive 10 euro for the single blood sample.

# ADMINISTRATIVE ASPECTS AND PUBLICATION

# 11.1 Handling and storage of data and documents

All study data will be registered in a collection of files (the source documents). Separate records will be commenced for each participant. All clinical data on participants obtained from the handling, treatment and observation will be recorded on Case Report Forms (CRF). Personal identifiers will not be recorded on the CRF, with exception of date of birth, initials, postcode and gender. The Principal Clinical Investigator assures that the anonymity of the participants is maintained; keeping separate log of codes, names and addresses of participants. The CRF forms the basis for further analysis of the study results. The contents of the CRF are summarized in annex 2. To enable efficient data analysis, electronic data files will be compiled. Source documents and hard copies of electronic files/analyses will be stored according to GCP guidelines (for a period of 15 years).

The CRF will contain information obtained according to the study assessments described in Chapter 4. The sponsor investigator is not entitled to know personal data of the participant. Thus, the principal clinical investigator is required to separate personal and study data on the CRF. Throughout the CRF, on every page, the UTN number will be used as the unique participant identifier. Furthermore, date and time of study procedures and assessments will be recorded throughout the CRF for all recorded observations.

Data registered in the source documents will be made available for analysis in electronic data files. To establish a validated data set for analysis, a procedure of entry and verification will be used. All necessary changes and corrections after data entry will be motivated, dated and signed by the investigators.

Data analysis will be done by the sponsor investigators. Validated data sets will be used for analysis. All obtained data will be used for intention to treat analysis.

The study results will be reported in an internal report and submitted for publication in peer-reviewed journals. Publications will be drafted by the sponsor investigators.

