# 5 TREATMENT OF SUBJECTS

## 5.1 Investigational treatment

#### Children of 8-9 years old will be asked to receive an extra pertussis-component in the DT-IPV booster vaccination (DT*Pacv*-IPV) together with their MMR vaccination. There will be no extra injection, only a change in vaccination composition (addition of the pertussis component). Pre- and post-vaccination a blood sample of 15 ml will be taken by venous puncture. Post-vaccination blood sampling will be done at 28 days (± 2 days) and 1 year (± 2 weeks) after the booster vaccination. To examine *B. pertussis* specific memory B- and T-cells we need a minimum of 1 x 106 Peripheral Blood Mononuclear Cells (PBMC's) to analyse one of the 5 most important *B. pertussis* specific antigens (Ptx, Prn, FHA, Fim 2 and 3). B- cells account for only 2 to 10% of all PBMC's and only 20-30% of all B- cells are memory B- cells. On average we can isolate 1 x 106 PBMC's per ml blood, however this is highly variable per person. To analyse specific memory B- cells to all 5 *B. pertussis* antigens, an amount of 15 ml blood is needed. With less material, B- cell responses against just one or two proteins of *B. pertussis* (Ptx, Prn or FHA) will be measured. In our ongoing study a blood sample of 15 ml is not a problem in 8-9 years old children.

##

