# METHODS

## 7.1 Study parameters/endpoints

#### 7.1.1 Main study parameter/endpoint

The main study parameters will be the longitudinal kinetics of B- and T- cell memory immune responses and antibody responses against the vaccine proteins of *B. pertussis*.

Blood samples will be separated in Peripheral Blood Mononuclear Cells (PBMC's) and plasma samples. PBMC's will be divided in purified B- cell populations and T- cell populations.

B- cells will be cultured and memory B- cells will be polyclonal stimulated (Bernasconi et al, 2002). After 5 days stimulation, B- cell memory responses will be measured against the various proteins of *B. pertussis* (FHA, pertactin, PT, Fim 2 and 3) by ELIspot assays and MIA (Multiplex Immuno Assay) or ELISA of the culture supernatants.

The plasma samples will be used to measure antibody responses against the various proteins of

*B. pertussis* (PT, PRN, FHA, Fim 2 and 3), and, if necessary to the extra components of the National Immunization Program. IgG and IgA antibody titer is measured in

multiplex immuno assay (MIA) (Gageldonk et al 2008) in two dilutions using FDA reference

serum as standard (EU/ml, Meade et al 1995).

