## Randomisation, blinding and treatment allocation

No randomization or different treatment groups are designed in this study.

Personal data

Personal (identity) data are defined as the set of data that together might disclose the identity of a participant: name, date of birth, sex, and full address. The principal clinical investigator will guarantee that personal data from participants are treated anonymously, unless medical conditions of the participants require release of anonymity.

Study data

Study data are defined as the set of all participant-related variables such as: initials, postal code (only the four numbers), vaccination status, data on possible adverse events, antibody data. The storage of data is such that third parties have no access to the data.

- Data on the CRF

On the CRF the following data must be written:

- UTN (unique trial number)

- number of vial

- expiration date

- place of administration (left or right arm)

- name, date, signature of the person who have given the vaccination.

- remarks

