### Specific criteria for withdrawal (if applicable) not applicable

## Replacement of individual subjects after withdrawal

## Because we expect 15% of all children to prematurely withdraw from the study, we aim for 70 children at the start of the study, so there will be 60 children completing the study. For the control group we aim for 20 children.

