**9.** **STATISTICAL ANALYSIS**

## Descriptive statistics

Since nothing is known about cellular immune responses against *B. pertussis* in the Dutch population, data of these responses after the booster vaccination with DTPacv-IPV at 8-9 years as well as in the control group will be presented in descriptive statistics, including frequency tables and charts. Descriptive statistics will mainly constitute measures of central tendency (e.g. mean) and measures of dispersion (e.g. range and standard deviation). Antibody levels against the different pertussis antigens will be described in figures and geometric means will be calculated. Differences between the antibody levels pre- and post vaccination will be analysed with a paired t-test. The cellular responses will also be described in figures. Correlations will be measured between the cellular responses and the antibody levels.

Considering the number of children who are already included in the previous study (60 participants) and the expectation of 15% of the children will quit the study prematurely, we aim for 70 children.

The number of 60 children per age group in the former Memory study, is calculated as follows:

To be able to describe significant differences in serological responses between groups or time-points per group, the size of the study groups is dependent on the number of data available from former studies with the “old” WCV and the observed mean antibody titers against the pertussis vaccine components. Data from the DTPwcv/Hib “mixture” study performed in 1993-1994 (Labadie et al 1996) are available from 90 samples. If we combine these data with results from MMR studies (also pertussis measured) a total of 268 data are available. Inclusion of 45 children in each group in this study would mean that there has to be a 2.3-fold rise in mean antibody titers for antibodies against PT and a 2.0-fold rise in that for PRN between groups (power of 90% and a significant level of 5%) using data from the DTwcP/Hib mixture study only (n=90). If also the other available data (n=268) are included these titer rises would become 2.1-fold for PT and 1.8-fold for PRN needed to detect a significant difference with the same power and level. Recent experiments has clearly indicated that at 28 days after vaccination significant differences in antibody responses were found between groups consisting of 35 children of 4 years, which had received either Triaxis or Infanrix-pertussis as a booster vaccine.

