Considering the available time span and the area’s where the study has to be performed it is realistic to aim for 45 children per group. Anticipating withdrawals and dropouts during the trial the objective is to include 60 children per group. This will allow us to observe a statistically significant difference between the different time-points before and after booster vaccination if we measure a twofold rise in the antibody titer against these antigens of the pertussis vaccine component.

For the control group we aim for 20 children who did not receive the extra ACV booster at age 8-9 years and who have the same age as the children under investigation in the study. One bloodsample will be taken one year after the regular DTP vaccination to exclude the effect of *Bordetella pertussis* circulation on the immunological parameters measured. Since pertussis antibody levels wane in 2-3 years after vaccination, high antibody levels will indicate a recent infection with *Bordetella pertussis* in this control group. For comparison of the results of the children who received the extra pertussis vaccination with this control group one-year post-vaccination, we will use an unpaired t-test. Antibody levels and cellular responses will be described in descriptive statistics and figures. In this way, we can improve the understanding of the vaccine effect on the immunological parameters measured.

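### Antibody kinetics over three samples are tested only by a pre v post paired t-test, so a one-year contrast would rest on completers; one repeated-measures model would use every sample

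*Protocol*

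**What the plan says.** Four statements in the protocol bear on this.

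- **Main parameter (Section 7.1.1).** "The main study parameters will be the longitudinal kinetics of B- and T- cell memory immune responses and antibody responses".
- **Sampling (Section 5.1).** There is one sample before vaccination, and then: "Post-vaccination blood sampling will be done at 28 days (± 2 days) and 1 year (± 2 weeks) after the booster vaccination".
- **Analysis (Section 9.1).** For antibodies: "Differences between the antibody levels pre- and post vaccination will be analysed with a paired t-test". The text does not say whether the post sample is day 28, one year or both. For cell responses: "The cellular responses will also be described in figures". For the one-year comparison with the control group: "we will use an unpaired t-test".
- **Data used (Section 11.1).** "All obtained data will be used for intention to treat analysis".

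On losses, Sections 4.4, 7.5 and 9.1 expect 15% of children to stop early. The plan enrols 70, "so there will be 60 children completing the study". Section 7.6 provides no follow-up after withdrawal. On allocation, Section 7.2 says: "No randomization or different treatment groups are designed in this study".

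**The concern.** A paired t-test uses a child only if both samples of the pair exist. For a contrast of one year with baseline, a child who left after day 28 contributes nothing, although two of that child's three samples are in hand. This sits poorly with a statement that all obtained data will be used. It also sits poorly with a main parameter that runs over all three visits, because the early rise would be estimated in one set of children and the one-year result in a smaller one.

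Two things are at stake. The first is some precision at one year. The second is what the one-year figure describes: if leaving is related to the day-28 response, a completers' estimate is shifted, whereas an analysis that uses the day-28 values can correct for it.

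Separately, intention to treat refers to keeping participants in the group to which they were allocated. Nothing is allocated here, so the term does not define an analysis set.

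**Working it through.** **1. The plan's own figure.** For 60 completers with 15% loss: 60/(1 − 0.15) = 70.6, that is 71. In the other direction, 70 × 0.85 = 59.5. The stated 70 is reproduced to within one child. The expected number without a one-year sample is 70 − 60 = 10, or 10/70 = 14%.

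**2. Assumed inputs.** The protocol gives no SD of log titre and no within-child correlations.
- *SD.* Section 9.1 quotes a 2.3-fold difference for PT with 45 per group, 90% power and a 5% level. Taken as two-sided, SD = log10(2.3)/[(1.960 + 1.282) × √(2/45)] = 0.3617/0.6834 = 0.53.
- *Correlations.* These are assumptions. Write r12 for pre and day 28, r13 for pre and one year, and r23 for day 28 and one year.

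**3. Power cost of the loss.** Power of the paired t-test (noncentral t) for a twofold change with SD 0.53:

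| Correlation | n = 60 | n = 70 |
|---|---|---|
| 0 | 86% | 91% |
| 0.3 | 96% | 98% |
| 0.5 | 99% | 100% |

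Against no loss at all, the confidence interval is √(70/60) = 1.08 times as wide. No analysis recovers all of that.

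**4. What using all samples recovers if loss is random.** Let D be the one-year minus pre log10 difference and R² the share of its variance explained by the pre and day-28 values. The all-data variance divided by the completers' variance is about 1 − R² × (fraction lost).
- With r12 = r13 = 0.5 and r23 = 0.7, the regression weights for the one-year value are 0.20 (pre) and 0.60 (day 28). Its residual variance is 1 − (0.20 × 0.5 + 0.60 × 0.7) = 0.48 in units of SD². Var(D) = 2(1 − 0.5) = 1, so R² = 0.52.
- Variance cut: 0.52 × 10/70 = 7.4%, or 0.52 × 0.15 = 7.8%. A simulation of 70 children with about 15% loss gave a variance ratio of 1.09, a cut of 1 − 1/1.09 = 8%.
- With all three correlations at 0.5, R² = 1/3 and the cut is 0.333 × 0.15 = 5%. So 8% is not a floor.

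**5. What happens if weak day-28 responders leave more often.** In a simulation, one-seventh of children leave after day 28, with r12 = 0.3, r13 = 0.5 and r23 from 0.3 to 0.8. The table gives the completers' estimate divided by the truth.

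| Dropout mechanism | One year/pre | One year/day 28 |
|---|---|---|
| Random | 1.00 | 1.00 |
| Odds of leaving double per SD lower day-28 titre | 1.00 to 1.06 | 0.92 to 0.98 |
| Only the lowest one-seventh leave | 1.00 to 1.18 | 0.80 to 0.94 |

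An estimate of the one-year level that also used the pre and day-28 values was within 0.5% of the truth in every scenario. A second simulation, with correlations 0.5 to 0.7 and a true one-year/pre ratio of 10^0.4 = 2.51, gave 2.60 and 2.63 from completers (1.04 and 1.05 times truth) and 2.51 from all data.

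**6. The shift against sampling error.** The shift from 2.51 to 2.60–2.63 is 0.015 to 0.020 on the log10 scale. The standard error at n = 60 is 0.53 × √(2 × 0.5)/√60 = 0.068 at correlation 0.5 and 0.53 × √(2 × 0.3)/√60 = 0.053 at 0.7. The shift is therefore 0.015/0.068 = 0.2 to 0.020/0.053 = 0.4 of a standard error.

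**The case against.** The case for leaving the plan alone is a fair one.

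- **A reader might infer that every child without a one-year sample is discarded.** The protocol does not say so. Such a child stays in the pre v day-28 test, the geometric means, the figures and the correlations. This objection stands.
- **A reader might infer that Sections 9.1 and 11.1 contradict each other.** Section 11.1 is one sentence on data handling. It can be read as saying that nothing obtained is excluded, not that each sample enters each test. The descriptive part of Section 9.1 can honour it. This stands too: the method fits the statement poorly but does not break it.
- **The paired t-test covers antibodies only.** Cell responses are described without a within-child test, and no day-28 v one-year test is named. The point must be limited accordingly.
- **The loss is planned for.** Enrolling 70 for 60 protects power. It does not change whom the one-year contrast describes.
- **The bias is hypothetical.** Nothing links withdrawal to titre; Section 7.4 lets parents withdraw for any reason.
- **Missing-sample handling often belongs in an SAP, which is not shown.** That is so, and the absence of such detail is not the point. The protocol itself names the test, and a better one is available at almost no cost.

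**Conclusion.** The point holds as an improvement in method, not as an error or a contradiction. A one-year paired antibody contrast would describe about 60 of 70 children and leave unused the earlier samples of about 10. A single repeated-measures analysis fits three-visit kinetics and the all-data statement better.

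The gain is modest: up to about 8% in the variance of the one-year/pre fold change at the assumed correlations, and about 5% if all of them are 0.5. The stronger conclusion that the plan will misstate persistence is not supported. It needs dropout related to response, which the protocol does not suggest. Even under a moderate version, the ratios move by a few per cent, about 0.2 to 0.4 of a standard error for one year/pre, and in opposite directions for the two one-year ratios. The larger distortions arise only if exclusively the weakest responders leave. All of these sizes rest on the assumed SD, correlations and dropout mechanisms.

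The intention-to-treat label is misplaced in a study without randomisation, but correcting it alone changes no result.

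**What to change.** - **Section 9.1, antibody levels.** Fit one linear mixed model per antigen to log10 values, with visit (pre, day 28, one year) as a fixed factor and an unstructured within-child covariance. Include all vaccinated children with at least one sample. Report the fold changes day 28/pre, one year/pre and one year/day 28 with 95% confidence intervals. This also settles which post sample is meant.
- **Sensitivity analysis.** Keep the paired t-test on children with both samples. With complete data the model gives the same mean differences, so any gap between the two shows the effect of the missing samples.
- **Section 11.1.** Replace the intention-to-treat wording with that analysis set.

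The cost is a little more analysis work; no extra visits, blood or children are needed. The model relies on loss being missing at random given the observed titres. It does not protect against dropout that depends on the unseen one-year value.

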## Amendments

A ‘substantial amendment’ is defined as an amendment to the terms of the METC application, or to the protocol or any other supporting documentation, that is likely to affect to a significant degree:

- the safety or physical or mental integrity of the subjects of the trial;
- the scientific value of the trial;
- the conduct or management of the trial; or
- the quality or safety of any intervention used in the trial.

All substantial amendments will be notified to the METC and to the competent authority.

Non-substantial amendments will not be notified to the accredited METC and the competent authority, but will be recorded and filed by the sponsor.

This is the first amendment of this study. The changes are:

- Change in our reference: LIS142 (instead of LIS/IMM138)

- The inclusion of a control group consistent of 20 children of the same age as the participants, but who received the regular DTP vaccination and did not receive the extra ACV booster vaccination at 8-9 years of age.
- The newsletter that we would like to sent to each participant of the Booster study (annex 1)
- The extra information for the control group (annex 2)
- The informed consent form for the control group (annex 3)
- The CRF for the control group (annex 4).
- The question list for the control group (annex 5)

